9. HUMAN SUBJECTS

There will be two groups of participants in this study: (1) CBO personnel and (2) FSWs recruited into the *Mujer Segura* intervention study.

***CBO Staff***

The primary participants will be CBO personnel, including staff who will deliver the intervention, their supervisors, and local directors (12 CBOs, approximately 10 personnel per site = 120). Twelve CBOs affiliated with MexFam will be enrolled into this project. We expect that some of the smaller clinics may not be able to provide a quota of 10 staff. Accordingly, to ensure that we recruit the desired minimum the entire study, we request flexibility in the per-clinic figures to enable us to recruit more than 10 if opportunity affords, up to a maximum of 135 staff for the entire study.

The CBO staff who participate in the organizational-level portion of this study will be recruited based upon their institutional role. MexFam’s executive leadership will make it clear to all staff that although the intervention study with FSWs is part of MexFam’s mission and hence is something to which all staff will be expected to contribute if necessary, the organizational-level study (individual interviews, focus groups) is entirely voluntary, and that no adverse consequences will follow upon a decision not to participate. A modest financial incentive, over and above the potential participant’s normal salary (which he or she will also receive for the approximately 6 hours total time spent on activities related to the part of the study) will be offered to encourage participation (see Section 18).

***Intervention Study Participants (FSWs)***

The second set of participants in this research will be the FSWs who are recruited at each CBO to participate in the baseline and follow-up assessments and either the *Mujer Segura* counseling intervention or the “usual care” comparison condition. The recruitment goal for the study will be 960 female sex workers (FSWs) from the twelve anticipated sites (12 CBOs times 80 FSWs per site = 960). As with the staff participants (see above), we are uncertain whether the all of the currently projected sites will be able to meet this quota. We also face the uncertainty (particularly in the early phases of the study) whether, once the study has been started at a particular site, the staff will be able to carry it to completion due to factors beyond our or Mexfam’s control. Accordingly, we request flexibility in the per-clinic and overall figures for recruiting FSWs, up to a maximum of 1,090 for the entire study (in increase of 130, which is 13.5% more, or the equivalent of less than two additional sites).

We anticipate that participants will range in age from 18 to 50 years (mean approx. 33); mean level of educational attainment will be 6 years; 80% will be married or living in a common-law relationship; and 94% will have children.

Inclusion Criteria: To be eligible for this intervention, participants must be:

1) Biologically female,

2) At least 18 years old,

3) Report having exchanged sex for money, goods or drugs within the previous 30 days,

4) Report having unprotected vaginal or anal sex with a male client at least once during the previous month.

Exclusion Criteria:

1) Consistent use of condoms for vaginal and anal sex with all male clients during the previous month,

2) Known to be HIV+ or test HIV+ for the first time on-site at MexFam clinic,

3) Being under 18 years of age,

4) Being male or transgendered,

5) Being incapable of giving informed consent,

Because this study is designed to transport an established, efficacious intervention into a community-based setting, we must adhere to core elements of the established intervention, which was designed for women who are biologically female. In the original intervention design, transgendered persons were excluded because this subpopulation of FSWs would require different recruitment strategies and a targeted intervention to reflect unique sexual risk behaviors and sexual milieu.

10. RECRUITMENT

***CBO Staff***

The Executive Director of MexFam or his representative will ensure that, prior to implementation of the study, all eligible clinic staff are given an overview of the project that carefully distinguishes between the intervention study component (which is congruent with MexFam’s mission to protect and improve the health of vulnerable populations and, as such, has a claim on all employees’ involvement as part of their normal job duties) and the organizational-level component of the study, for which the employees’ informed consent is required prior to their enrolling as participants. The Executive Director will ensure that all employees understand that their participation in the organizational-level part of the study is voluntary, and that their employment status or compensation will not be affected by a refusal to participate. The study’s ethnographers will then visit each CBO and invite eligible staff (those who will deliver the intervention, their supervisors, and the clinic’s director) to participate.

***FSW Intervention Participants***

Participants will be recruited from designated areas in which sex work occurs in the city where the CBO is located. Based on our experience, sex work venues include bars, hotels, street corners, massage parlors and brothels. FSWs will be approached in the field by trained outreach workers who will ascertain the participant’s willingness and eligibility to participate in the study through the use of six screening questions (no identifiers on form) asked in a conversational manner. FSWs who are potentially appropriate for inclusion and willing to participate in the study will be referred to the participating MexFam clinic (transportation will be provided as needed).

11. INFORMED CONSENT (Note: provide information in Section 28 on Surrogate Consent and Decisional Capacity Assessment, if applicable)

***CBO Staff***

The study’s ethno­graphers, having identified staff who are willing to participate in the organizational-level component of the study, will review the informed consent document with them, which contains all pertinent information regarding study procedures, risks and benefits, safeguards for confidentiality, and compensation. Potential participants who still have questions after these explanations will be put in touch with [name] or [name].

***FSW Intervention Participants***

The informed consent procedure is designed to maximize the potential participant’s comprehension of study procedures and to ensure that participation is voluntary. Before a participant is enrolled, the purpose, the procedures to be followed, and the risks and benefits of participation will be explained by project staff, and signed informed consent from the participant will be obtained. To obtain informed consent from women who are illiterate, a two-step solution was suggested by the Director of the UCSD HRPP ([name]) and UCSD ethicist, [name]: 1) consent forms are read out loud, and 2) a simple test is given wherein participants are questioned about points made in each paragraph of the consent (e.g., “How much time will this take you?”; “What are the possible benefits for you?”). When errors are encountered, the paragraph is re-read and participants are encouraged to ask questions to clarify. They are retested to ensure they understand all passages. If, after further attempts to clarify any misunderstandings, project staff determine that a potential participant may not fully comprehend the critical aspects of the study, that potential participant will not be enrolled. If a potential participant decides she does not wish to participate, her decision will be honored regardless of how well she comprehends the study information. This process worked well through all five years of our *Mujer Segura* study (Project #051182).

12. THERAPEUTIC ALTERNATIVES (therapeutic studies only)

Since the desired primary outcomes of the intervention study with FSWs are increased use of condoms with clients and decreased incidence (i.e. prevention) of HIV and STIs, FSWs who are considering enrollment in the study will be informed in the consent document of alternative methods for decreasing their sexual risk behavior and HIV and STI risk.

Treatment of incident HIV and STIs is not a focus of the study; however, FSWs who enroll and who test positive for HIV or an STI are eligible under Mexico’s national health insurance program to receive free treatment at the municipal clinic in each participating city. All FSWs testing positive will be referred to the appropriate clinic for treatment.

13. POTENTIAL RISKS

***CBO Staff***

The risks likely to be encountered by clinic staff by participating in the one-on-one qualitative interviews and focus-group meetings are minimal. Participants may experience boredom or minor irritation at the nature of some of the questions asked. There is also a slight risk that a subject’s candid responses to questions about the organization may become known to clinic management and that management, contrary to organizational policy, may attempt to retaliate against subjects offering negative assessments of their organization or their employment situation.

In view of recent increases in drug-related violence in various parts of Mexico, CBO staff who go into the field as recruiters may incur an increased risk of finding themselves unexpectedly in harm’s way.

***FSW Intervention Participants***

The FSWs who enroll in the *Mujer Segura* intervention study face the following risks:

1) Bruising or fainting as a result of the venipuncture. These risks are deemed negligible, due to the training and experience of the clinic personnel (nurses, trained phlebotomists) who will perform the venipuncture.

2) FSWs who obtain a positive HIV test may experience the loss of a sex work permit (in localities where such permits are required), stigmatization, loss of private insurance (public health care is available to all Mexicans at no charge), loss of employment, loss of freedom to travel to some countries, loss of relationships with family, spouse, or friends, and anxiety or depression concerning their health, the health of their children, and their sexual partners.

3) Emotional distress due to the personal nature of many of the questions asked during the baseline and follow-up interviews.

4) Loss of confidentiality (i.e., a participant’s involvement of the study and hence her occupation as an FSW becomes known outside the study), which could result in loss of reputation or stigmatization. The risk of loss of confidentiality is deemed minimal based upon our experience with over 1,800 FSWs in our *Mujer Segura* intervention study (Project #051182), which used the same protocol and experienced no known breaches of confidentiality.

5) There is also some risk that counselors will receive reports of physical abuse and violence perpetrated against FSWs by clients or other sex partners. This is not a risk of the protocol per se, but rather an incidental result of it.

14. RISK MANAGEMENT PROCEDURES

***CBO Staff***

The risks of boredom or irritation during one-on-one interviews or focus group meetings have been minimized by keeping the length of each session to one hour or less. These risks will further be minimized by having the interviewer or focus-group leader assure the participants that they may refuse to answer any questions to which they object, and that they may request a short break at any time.

The risk of retaliation by clinic management for negative evaluations of organizational characteristics will be minimized in two ways: (1) MexFam’s Executive Director will clearly instruct all clinic directors that participant candor is to be encouraged and that no participant shall be penalized in any way for expressing his or her opinions, and (2) the organizational data (both quantitative and qualitative) will gathered and handled exclusively by ethnographers from the Cd. Juarez site, which is independent of MexFam. These data will not be shared with MexFam management unless the data have been de-identified both as to individuals and as to the site where the data were collected.

**Digital audio-recordings gathered from interviews with MexFam staff (counselors, directors, supervisors) will be stored on password-protected computers and identified by ID number only. Recordings will be transcribed as soon as possible and will be destroyed within two months after transcription. Counselor notes and worksheets will contain ID numbers only. These forms will be shredded at the completion of six-month follow-up. The key to participants’ code numbers (name-to-ID relational file) will be encrypted in a computer file, which will be locked in the director’s office at each MexFam CBO and in [name] office in San Diego. Only the CBO directors, Drs. [name] and [name], and the USCD data manager will be able to un-encrypt the computer file. Other security mechanisms at the MexFam CBOs and UCSD include: security workshops and written security policies and procedures.**

**The risks of inadvertent exposure on the part of recruiters to crime-related violence in the field will be addressed by ensuring that Mexfam’s existing security policies are carried out, which require that all new employees receive training in safety awareness and security procedures. Should conditions in the area around any of the Mexfam clinics give rise to increased concerns, the clinic director, in consultation with Mexfam’s executive director, will revise security procedures as necessary and promptly brief his or her employees.**

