***The Implementation Process: Organizational Level***

The implementation plan embraces four fundamental principles:

1) Developing local program expertise is important for sustaining model competency and fidelity. Involvement of model developers and practice experts should be front-loaded, then roles shift to local experts as they are developed.

2) Direct coaching and modeling in the actual practice setting is critical for optimal provider skill acquisition.

3) Maintaining and monitoring fidelity across time is critical. Adaptations to the local context or evolutionary changes in the model should be carefully planned, transparent and systematically implemented rather than made idiosyncratically or haphazardly.

4) Policy leadership and funding structures are important for institutionalizing the new practice model.

Phase One: Evaluation of Organizational Characteristics and Training of Staff and Delivery of Comparison Condition Intervention. Two trained ethnographers from the Ciudad Juárez training center will administer computer-based questionnaires to **ten staff (the director, intervention counselors, and supervisors).** The ethnographers will then conduct individual, semi-structured qualitative interviews with each participating staff member, and finally they will carry out a focus group session with all the participants at once in order to assess relevant provider and organizational factors. The questionnaires, the individual interviews, and the focus group session will all last about an hour each, and they will be tape-recorded. Provider factors to be assessed include: attitudes toward adoption of innovation (e.g., intuitive appeal of intervention program); personal disposition (e.g., adaptability, change catalyst); knowledge and perceived utility of intervention; and socio-demographic characteristics. Organizational factors include: leadership qualities; organization culture and climate (e.g., work attitudes, autonomy); organizational support (e.g., support for creativity); and social influence (e.g., teamwork). The same battery of assessments was used by [name] in a study of a children’s service agency (see [name], item 5 in Bibliography). A copy of that assessment battery is provided in Appendix 2. The measures have all been translated into Spanish, and the name of the organization has been changed to fit the new study.

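### The clinic director's place in the staff focus group, and access to the staff name-to-ID key, contradict the promise that management sees only de-identified staff data

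*Protocol*

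**What the plan says.** Section 13 (CBO Staff) describes a slight risk to staff who speak frankly: their "candid responses to questions about the organization may become known to clinic management". It then names the harm that could follow: "management, contrary to organizational policy, may attempt to retaliate against subjects offering negative assessments of their organization".

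Section 14 (CBO Staff) answers that risk in two ways:

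- MexFam's executive leadership instructs clinic directors to encourage candor, with the rule: "no participant shall be penalized in any way for expressing his or her opinions".
- The organizational data, quantitative and qualitative, are "handled exclusively by ethnographers from the Cd. Juarez site, which is independent of MexFam". A limit on disclosure follows: "These data will not be shared with MexFam management unless the data have been de-identified both as to individuals and as to the site".

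The next paragraph, still under CBO Staff, deals with the audio-recordings of staff interviews, which carry an ID number and no name. It says the name-to-ID key is "encrypted in a computer file, which will be locked in the director’s office at each MexFam CBO", with another copy in San Diego. The CBO directors are listed among those who can decrypt it, with two investigators and the UCSD data manager.

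Section 8 (The Implementation Process: Organizational Level, Phase One) gives the participants as "ten staff (the director, intervention counselors, and supervisors". After questionnaires and individual interviews, the ethnographers come to the group session: "finally they will carry out a focus group session with all the participants at once". The organizational factors to be assessed include leadership, culture and climate. Phase Three repeats the interviews and focus groups at the end of implementation.

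**The concern.** The second safeguard in Section 14 is a barrier between what staff say and the people who manage them. The clinic director is the nearest member of that management, yet the plan puts the director on the wrong side of the barrier twice: in the room when the group talks, and among the holders of the key.

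Two things are at stake. The first is the assurance to staff. Section 11 says the consent document covers safeguards for confidentiality, so staff would be agreeing to a protection that the procedures do not fully deliver. The second is the quality of the organizational data. Aim 2 depends on frank accounts of leadership, culture and climate, and people speaking in front of their director may hold back.

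**Working it through.** No sample size, power or event count enters this point, so the check sets the provisions side by side.

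**Step 1: is the director a participant?** Yes. Section 8 (Phase One) lists the director, and Sections 9 and 10 both include clinic directors among the staff to be enrolled or invited. No section excludes the director from any session or separates staff by rank.

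**Step 2: what does a joint focus group do to the promise in Section 14?** The promise works through de-identification before anything reaches management. A director who is present hears who said what before any record exists to de-identify. For this data source the promise cannot be kept, and the session is held twice, at the outset and at the end.

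**Step 3: what does the key add?** Staff recordings carry only an ID number, so their anonymity rests on the key, and the director can decrypt it. But the key alone reveals no answers. Linking a named person to an answer takes two things:

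- the key, which the director can open; and
- the ID-labelled data, which Section 14 reserves to the ethnographers.

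One of two barriers is removed and the other stands. Questionnaires and individual interviews are therefore less well protected, but not exposed.

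**Step 4: which data could be affected?** Section 8 (Phase One) orders the baseline work as questionnaire, then individual interview, then focus group. Baseline questionnaire answers are thus given before the joint session and not in front of the director. Hypothesis 2a and the other quantitative Aim 2 hypotheses are tested by regression, correlation and mediation. The focus-group material goes into the qualitative analysis, which is meant to complement those results. The direct effect therefore falls on the qualitative material. Section 18 pays staff for completing the same set of assessments at follow-up. On that reading, a second questionnaire would come after the first joint session, so an indirect effect there cannot be ruled out.

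**Step 5: how many people?**

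- Staff planned: 12 CBOs × 10 = 120.
- Directors, assuming one per CBO: 12.
- Other staff: 120 − 12 = 108.

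The 10 per site is approximate, and Section 9 asks for leave to enrol up to 135 in all. The 108 counts staff to whom the provisions apply; it does not count staff whose answers would be disclosed.

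**The case against.** The strongest reply has several parts.

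- **The first safeguard is untouched.** The instruction to directors not to penalise candor does not depend on who holds the key or who attends the group. This stands. It does rely on compliance by the people concerned, and Section 13 already allows that management might act against policy.
- **The risk is rated slight.** This stands, and it bears on severity. It does not remove the contradiction.
- **The key sentence may be copied text.** It recurs word for word in Section 14 (FSW Intervention Participants). In the staff paragraph it follows a line on counselor notes to be shredded after six-month follow-up, which is the FSW visit schedule. That is plausible. As printed under CBO Staff, directly after the staff recordings, it still governs staff, so at the least it needs clarifying.
- **Participation is voluntary.** A director might decline, any participant may refuse a question, and the individual interview is a channel without the director. All true, but the plan includes the director by design.
- **Supervisors are in the group too.** Removing only the director leaves counselors speaking in front of their supervisors. This is a fair limit on the remedy.

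A reader might infer that the whole protection against retaliation is defeated, or that directors can link every answer of 108 staff to a name. The documents do not support this: the key gives no answers without the data, and the first safeguard remains. A reader might also infer that the culture, climate and leadership scores in Aim 2 will be shifted upward and compressed. No section shows that staff are told who holds the key. A uniform upward shift would not by itself change associations, and compression would need a ceiling effect that nothing in the protocol documents.

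**Conclusion.** The contradiction is real and lies within the protocol. In the focus group, the promise that management receives only de-identified data fails whenever the director attends. For questionnaires and individual interviews, director access to the key weakens the protection without defeating it.

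The provisions apply at all 12 sites and twice per site for the focus group. The clearest consequence for the data is guarded talk in the qualitative focus-group material. Bias in the quantitative Aim 2 measures is possible, but neither its size nor its direction can be derived from the documents. The conclusion assumes that the key sentence under CBO Staff applies to staff, as printed, and that directors take part as planned. If the sentence was copied by mistake, the focus-group half still holds.

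Severity is moderate. Randomisation, power and the FSW outcomes are unaffected, but a stated human-subjects assurance should match the procedures.

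**What to change.** 1. **Section 14 (CBO Staff):** remove the CBO directors from those able to decrypt the staff key, and remove the copy kept at each CBO. Hold the staff key only at UCSD, with the investigators and the data manager. It should not pass to the ethnographers, because they hold the ID-labelled data and key and data should stay apart. If directors need access to a key, limit this to the FSW key in Section 14 (FSW Intervention Participants), and state that the two keys are separate files.
2. **Section 8 (Phase One, and the repeat in Phase Three):** hold the staff focus group without the clinic director, whose views are already collected by questionnaire and individual interview. The text should also say openly that supervisors remain in the group.

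The cost is a short amendment and a change in file access, with no added session, staff or analysis. The one loss is the director's contribution to the group discussion.
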